**III.c. Study Variables**

III.c.1. Dependent variables

The following variables will be evaluated: neuropsychological outcome (Go/ No tasks); power analysis of frequency bands through QEEG; and brain reconstruction network model of each individual by QEEG.

III.c.2. Independent variables

Transcranial direct current stimulation and sham procedure.

**III.d. Procedures**

After screening through psychiatric interview, explanation about all steps of this study, and agreement expressed through signed informed consent form, ADHD patients will underwent a cognitive evaluation through the Mini-mental state examination (MMSE), Mini International Neuropsychiatric Interview Brazilian (MINI PLUS), Adult Self-Report Scale (ASRS), Quality Questionnaire life in Adults with ADHD (AAQoL), and an interview through a questionnaire. This evaluation script is an instrument based on the ADHD diagnostic criteria from DSM-IV-TR, and consists on epidemiological and clinical questions.

Individuals will be divided into two groups by block randomization, aiming at a balanced distribution between the groups (30 subjects each). Blocks shall be composed of 10 subjects, totaling six blocks. To compose each group will be called 5 individuals from each block.

Following it, the brain electrical activity will be recorded by EEG with 32 channels placed on the scalp acoording to the 10-20 EEG international system, during 5 minutes. The recording will be in a resting state, the first minute with eyes open looking for a fixed point, and the last 4 minutes with eyes closed. Then, participants will be asked to perform tasks on the computer: two Go / No go tasks adapted from the original version, the first using as a target a fruit and the second a letter. After the cognitive tasks, subjects will undergo active or sham stimulation, according to the previous randomization.

Participants of the intervention group will be submitted to tDCS at 1mA, anodal electrode over the left dorsolateral prefrontal cortex and cathodal electrode over the equivalent area on the right side. On control group subjects (sham group), electrodes will be placed at identical positions and sham stimulation will be applied. The stimulation device will turn on for only 30 seconds so that the patient will feel the initial sensation, then shutting down. The intervention and sham procedure will take place in one single session of 20 minutes to evaluate the immediate effect.

At the end of the intervention, subjects will perform again two Go/ No go tasks (randomly selected to avoid learning effect), and they will undergo another EEG recording, with the same previous technical caracteristics.

This study will be performed at Laboratory of Functional Electrostimulation at Federal University of Bahia.

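### The arm is assigned from fixed, published blocks of 10 before the baseline EEG and Go/No-go tasks, with no stated concealment or staff masking, so the baseline could be taken with the arm known

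*Protocol*

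**What the plan says.** All of the allocation detail is in Protocol section III.d (Procedures). The method is stated first: "Individuals will be divided into two groups by block randomization, aiming at a balanced distribution between the groups (30 subjects each". The block scheme follows: "Blocks shall be composed of 10 subjects, totaling six blocks. To compose each group will be called 5 individuals from each block". Block size, number of blocks and split are thus constant and printed in the protocol.

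The same section gives the order of steps. Consent, MMSE, MINI Plus, ASRS, AAQoL and the interview are described before randomisation. The baseline recording is described after it: "Following it, the brain electrical activity will be recorded by EEG with 32 channels". The baseline tasks come next: "Then, participants will be asked to perform tasks on the computer: two Go / No go tasks". Stimulation is last: "After the cognitive tasks, subjects will undergo active or sham stimulation, according to the previous randomization".

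On sham, the section says: "The stimulation device will turn on for only 30 seconds so that the patient will feel the initial sensation, then shutting down". The stated purpose concerns what the patient feels. The section does not say who or what ends the current.

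Blinding is otherwise mentioned only in III.e, Step 5, as a chi-square test of its effectiveness, without saying who is blinded. Section III.f, on bias, covers diagnostic criteria and the validity of the scales. It does not mention allocation concealment or masked staff.

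**The concern.** Two features of the stated procedure combine badly.

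First, the arm exists before the baseline is measured. Section III.c.1 names Go/No-go performance, QEEG power and the QEEG-based network model as the dependent variables, and III.e Step 4 compares them before and after intervention. The baseline for all of these is taken after allocation. If the person giving the task instructions or recording the EEG knows the arm, instruction and encouragement at baseline can differ between arms. That difference passes directly into the before/after change.

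Second, a fixed, published block size lets anyone who has seen the earlier allocations in a block predict later ones. Entry depends on referral, advertisement and a psychiatric interview (III.b, III.d), so there is some discretion over who enters and when. With 30 per arm, a few steered entries could matter.

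This is not a detail that a statistical analysis plan would normally settle. The order of procedures and the randomisation method belong in the protocol, and this protocol fixes both.

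**Working it through.** **Inputs (Protocol III.d).** Block size 10; 6 blocks; 5 per arm per block; 30 per arm.

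**The plan's own figures.** 6 × 10 = 60 in total and 6 × 5 = 30 per arm. The scheme reproduces exactly.

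**Order of steps.** Set side by side, III.d gives: (1) consent and scales; (2) block randomisation; (3) baseline EEG; (4) two baseline Go/No-go tasks; (5) active or sham stimulation under the randomisation already made; (6) repeat tasks and EEG. Steps 3 and 4 supply the baseline of every before/after comparison, and both follow step 2. MMSE, ASRS and AAQoL fall in step 1 and are not affected by this part of the point.

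**Predictability of the blocks.** Assumption, not stated in the protocol: the observer knows the earlier allocations in the block. Write a block as 2m assignments, m per arm; here m = 5. All C(10,5) = 252 sequences are equally likely.

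- Assignments certain in advance, because one arm is used up: 2m/(m + 1) = 10/6 = 1.67 per block. Over six blocks, 6 × 1.67 = 10 of 60, or 16.7%.
- The last assignment of every block is certain. At least the last two are certain in 2 × C(8,3)/252 = 112/252 = 44.4% of blocks.
- Expected correct guesses, always guessing the less-used arm and tossing a coin when the counts are level: m + ½(4^m/C(2m,m) − 1) = 5 + ½(1024/252 − 1) = 6.53 per block. That is 65.3%, or 6 × 6.53 = 39.2 of 60, against 30 by chance.

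Full enumeration of the 252 sequences gives the same 1.67 and 6.53.

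**Would smaller, varying blocks help?** The same formulas give:

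| Block size | Certain per block | Correct guesses per block | Correct guesses, % |
|---|---|---|---|
| 4 | 1.33 | 2.83 | 70.8 |
| 6 | 1.50 | 4.10 | 68.3 |
| 8 | 1.60 | 5.33 | 66.6 |
| 10 (plan) | 1.67 | 6.53 | 65.3 |

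A list of 60 made of three blocks of 4, four of 6 and three of 8 (12 + 24 + 24 = 60) gives 3 × 2.83 + 4 × 4.10 + 3 × 5.33 = 40.9 correct guesses, or 68%. Hiding the sizes does not lower this, because the guess needs only the running imbalance, which returns to zero at the end of each block. Hiding them does cut the certain assignments: simulation with randomly chosen, undisclosed sizes of 4, 6 and 8 gives about 1.4 of 60 instead of 10, with the best guess again right about 68% of the time.

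**The case against.** The strongest reply is that the harm is read into silence. Assigning an arm is not revealing it. A concealed assignment, consulted only at stimulation, fits the wording of III.d, and randomising before baseline is not wrong in itself. The device could end the sham current automatically, so the 30-second description does not show an unmasked operator. Step 5 of III.e shows that blinding of some kind is intended. If all session staff were masked, the block size alone would reveal little.

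This stands against a stronger reading. A reader might infer that the operator is unmasked, is counting past allocations, and takes the baseline knowing the arm. The protocol neither says nor rules out any of this. The predictability figures are therefore conditional.

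Three further limits also stand. The wording about calling five individuals from each block may mean that ten people are gathered and then split, in which case predicting the next entrant matters much less. Computerised tasks and resting EEG limit staff influence, though they do not remove it. And 10 of 60 certain assignments measures predictability, not bias in an endpoint; five in six assignments are not certain even under full knowledge.

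What the reply does not remove is the order itself. The protocol states a sequence in which the arm is fixed before the baseline, and gives no safeguard that keeps it hidden until stimulation.

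**Conclusion.** The point holds as a weakness in the stated sequence, not as a demonstrated bias. The arm is set before the baseline EEG and baseline Go/No-go tasks, and no concealment or masking of session staff is described, so the baseline of every before/after comparison could be taken with the arm known. This part does not depend on how the blocks are filled.

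The sequence-guessing part rests on two assumptions: that staff know past allocations, and that participants enter a block one at a time. Under both, about 10 of 60 assignments are certain in advance and the best guess is right about 65% of the time. If staff are masked, or ten people are gathered and then split, the risk is smaller. The effect on any endpoint cannot be computed from the protocol.

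It is also tempting to conclude that the block size of 10 is itself the error and that smaller varying blocks would cure it. The figures do not support that, since overall guessability would rise. The change is worth making because it costs almost nothing and protects the baseline of all the stated outcomes.

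**What to change.** Change the step order in III.d. Complete the baseline EEG and both baseline Go/No-go tasks first. Then, immediately before stimulation, open that participant's concealed assignment, in a sealed envelope or as a code. Withhold the block size and the allocation list from staff who enrol and test participants.

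Keep the blocks of 10. Replacing them with blocks of 4, 6 and 8 would trade fewer certain assignments for a higher rate of correct guesses.

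The cost is a changed step order and the preparation of concealed assignments. No participants, visits or procedures are added. The total of 60, the 30 per arm and every other sample-size figure stay as they are.

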**III.b. Population**

Patients with attention deficit hyperactivity disorder will be recruited by letter and email to the Psychiatric Association of Bahia (APB), Bahia Neurology Society (SNB) and the Brazilian Association of Neurology, Psychiatry and Allied Professions (ABENEPI) - chapter Bahia. We will also contact by mail and telephone, professional experts in ADHD, inviting them to refer potential patients for the study. We will also publish advertisements on the internet and on social networks, from October 2012 to December 2012, according to the inclusion criteria.

III.b.1. Inclusion criteria

-Ability to understand and sign the informed consent form;

-Diagnosis of attention deficit-hyperactivity disorder according to DSM-IV-TR and Adult Self-Report Scale (ASRS);

-Residents in Bahia;

-18 years old or older;

III.b.2. Exclusion criteria

-Major psychiatric disorders such as schizophrenia and bipolar disorder;

-Inability to understand the questionnaires applied (cognitive impairment- score ≤ 24 on the Mini-Mental State Examination) or illiterate;

-Abuse of psychoactive substances or alcohol, except nicotine and caffeine, during the last 12 months.

III.b.3. Sample size

This will be a randomized sample of ADHD individuals recruited through Internet media, social networks, and contact with ADHD experts and specialized societies of neurology, psychiatry and related fields, during the study period. A sample size of 50 subjects was calculated assuming a difference in proportion between the active tDCS and sham control groups of 40% on the Go/ No go performance, before and after interventions.

This calculation was performed using the statistical program STATA 12.0, considering an alpha of 0.05 and a power of 0.80, resulting in an sample of 25 subjects in each group, intervention and control. To address unexpected factors, we applied a drop-out rate of 20%, reaching a total sample size of 60 individuals.

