**III.e. Statistical Analysis**

**Step 1**: socio-demographic, clinical and epidemiological description of the groups, using the usual procedures of descriptive statistics such as calculation of frequencies, measures of central tendency and dispersion;

**Step 2**: characteristics will be compared between groups at the baseline, using one-way analysis of variance (ANOVA) for continuous variables and chi-square test for categorical variables;

**Step 3**: Shapiro-Wilk test will be performed to assess normality assumption of the outcome variables;

**Step 4**: analysis of paired and independent samples using the t-test for comparison within each group and between intervention groups, or applying equivalent non-parametrics tests (according to Shapiro-Wilk test results), before and after intervention;

**Step 5**: Person's chi-square to evaluate blinding effectiveness, comparing between groups.

These analysis will be performed through Stata, version 12.0 for Windows. Results will be considered statistically significant if p ≤ 0.05.

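### Random selection of the Go/No-go tasks after stimulation does not remove practice, so within-arm change cannot be read as a tDCS effect; only the sham comparison controls for it

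*Protocol*

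**What the plan says.** Protocol III.d (Procedures) describes the baseline tests as "two Go / No go tasks adapted from the original version, the first using as a target a fruit and the second a letter". Stimulation or sham follows in "one single session of 20 minutes to evaluate the immediate effect". Afterwards, "subjects will perform again two Go/ No go tasks (randomly selected to avoid learning effect". The fruit and letter tasks are the only ones named. The section does not say whether the order of these two is randomised or whether tasks are drawn from a wider set of versions.

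Protocol III.e, Step 4, plans "analysis of paired and independent samples using the t-test for comparison within each group and between intervention groups", or non-parametric equivalents. The sham arm follows the same sequence: "electrodes will be placed at identical positions and sham stimulation will be applied". Go/No-go is the measure named in specific objective I.b.1 and is the basis of the sample size in III.b.3.

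**The concern.** The protocol gives a reason for the random selection, and the reason is that it avoids learning. A reader who accepts this would take a before-after gain within the active arm as the effect of stimulation, and Step 4 supplies exactly that test. If practice remains, a significant within-arm change is expected even when tDCS does nothing.

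A second, smaller matter is that the rule differs between the two times. Baseline is listed in a set sequence and the repeat is random. A participant may then do a given task in a different position before and after or, if other versions exist, a different task. That adds noise to the paired differences and weakens the link between baseline and post scores.

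**Working it through.** **1. The two possible readings of III.d**

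| Reading | What is random after stimulation | Practice | Before-after pairs |
|---|---|---|---|
| A | Order of the same fruit and letter tasks | Both tasks already done in this visit | Fruit-fruit and letter-letter exist for everyone; position changes for about half |
| B | Versions drawn from a wider pool | Item-specific learning may fall; familiarity with the go/no-go format remains | Content can differ |

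General practice survives under both.

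**2. Inputs**

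- From the protocol: 25 per group and alpha 0.05 (III.b.3). The 25 can be reproduced: a 40-point difference from 0.10 to 0.50, two-sided, power 0.80, with continuity correction, gives 25. The two rates are assumed because the protocol states only the difference. Nothing in this point changes that figure.
- Assumed, because the documents give no values: score SD 1, pre-post correlation r = 0.6, and the sizes of the practice, position and task-difference effects.

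**3. Within-arm test, no tDCS effect**

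Variance of change = 2(1 − r) = 2 × 0.4 = 0.80, so the SD is 0.894. For a practice gain m, the paired t-test has noncentrality m√25 / 0.894.

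| m (SD) | Noncentrality | Sham arm significant |
|---|---|---|
| 0.2 | 1.12 | about 19% |
| 0.3 | 1.68 | about 36% |
| 0.5 | 2.80 | about 76% |

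A simulation of 4,000 trials per setting gives the same percentages. The nominal rate is 5%.

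**4. Active versus sham**

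The same procedure applies to both arms, so practice adds the same amount to each and cancels in the difference. In the simulations the between-arm test of change rejected in about 4% to 6% of null trials in every setting, including those with a task difference of 0.5 or 1.0 SD affecting half the participants.

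The cost is variance. If a shift δ affects half the participants at random, it adds δ² × ½ × ½ = δ²/4 to the variance of change. For a true effect of 0.73 SD (chosen because it gives about 81% power with no shift):

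| δ (SD) | Variance of change | Power |
|---|---|---|
| 0 | 0.80 | about 81% |
| 0.2 | 0.80 + 0.01 = 0.81 | about 80% |
| 0.3 | 0.80 + 0.0225 = 0.8225 | about 80% |
| 0.5 | 0.80 + 0.0625 = 0.8625 | about 78% |
| 1.0 | 0.80 + 0.25 = 1.05 | about 69% |

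Simulation gave 77% at 0.5 and 70% at 1.0. Under reading A, δ is a position effect on a single task. In the mean of both tasks an additive position effect cancels, because each participant has one first and one second task at each time. Under reading B, δ is a difference in difficulty. It need not cancel, and a lower correlation between different versions would add further variance.

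**5. What baseline adjustment gains**

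Step 4 does not say whether the between-arm t-test uses post scores or change. With r = 0.6, the relevant variances are 1.00 for post scores alone, 2(1 − 0.6) = 0.80 for change, and 1 − 0.6² = 0.64 for ANCOVA. For the same 0.73 SD effect and 25 per arm, power is about 72%, 81% and 88%. The gain depends on comparing each task with its own baseline, which is what keeps r high.

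**The case against.** The strongest reply is that the trial's question is tDCS against sham, that both arms go through the same sequence, and that Step 4 includes the between-arm test. Within-arm tests cannot show efficacy in any pre-post design, however the tasks are chosen. The natural reading of doing two tasks again, when only two are named, is that both are given and only their order is random. Listing "the first using as a target a fruit and the second a letter" may even be plain enumeration rather than a fixed order. If new versions are meant, they could reduce item-specific learning, so the statement about learning would be partly right.

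Most of this stands. It rules out some stronger conclusions that a reader might draw:

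- That participants' differences compare fruit with letter. This needs a single random post task or a wider pool, and the text describes neither.
- That the draw is unbalanced between arms. The protocol is silent on balance, and a draw independent of arm is balanced in expectation.
- That there is a large loss of power. That depends on task content differing between times and on assumed correlations.

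The reply does not rescue the stated reason. Neither random order nor new versions remove practice with the go/no-go format, and the protocol both makes that claim and plans the within-group tests "for comparison within each group and between intervention groups" that would rely on it.

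**Conclusion.** The point holds in a limited form. The claim that random selection avoids learning is wrong for general practice under either reading, so the within-arm tests of Step 4 cannot separate practice from stimulation. Under the stated assumptions, modest practice gains of 0.2 to 0.5 SD would make the sham arm's own test significant in roughly a fifth to three quarters of trials.

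A reader might infer that the active-versus-sham result is biased. It is not, since practice is common to both randomised arms. The cost there is precision: about 1 to 3 percentage points of power per task for a position effect of up to 0.5 SD if only order varies, and about 11 to 12 points if half the participants met a post task differing by 1.0 SD. SD, correlation, effect size and shifts are all assumptions, and the protocol does not settle which reading applies.

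**What to change.** - In III.d, state that both the fruit and the letter task are given before and after stimulation. Counterbalance the order within arm from the randomisation list and keep it the same for a participant at both times. If other versions are intended, name the pool and the rule.
- Delete the bracketed reason about learning. State instead that practice is controlled by the randomised sham comparison.
- In III.e, Step 4, compare active with sham on each task's post score adjusted for the same task's baseline (ANCOVA), in place of unadjusted t-tests. Keep within-arm changes as description only and do not read them as a tDCS effect.

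The cost is one more column in the randomisation list, a few sentences and slightly more analysis work. Testing time does not change.

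### The within-group before-after EEG tests in Step 4 cannot isolate a stimulation effect, because the two resting EEGs sit at different points relative to the Go/No-go tasks; EEG conclusions should rest on the baseline-adjusted active-versus-sham comparison

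*Protocol*

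**What the plan says.** Protocol III.d (Procedures) sets the order of the session. A 5-minute resting EEG comes first, one minute with eyes open and four with eyes closed. "Then, participants will be asked to perform tasks on the computer", namely two Go/No-go tasks. "After the cognitive tasks, subjects will undergo active or sham stimulation, according to the previous randomization", and stimulation lasts 20 minutes in either arm. The post-stimulation step opens with the tasks: "At the end of the intervention, subjects will perform again two Go/ No go tasks (randomly selected to avoid learning effect". The repeat recording is named last in that same sentence: "they will undergo another EEG recording, with the same previous technical caracteristics".

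The order is therefore EEG, tasks, stimulation, tasks, EEG. The first links are explicit. That the second EEG follows the second task block rests only on the order of the sentence, and no interval between them is given.

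III.c.1 lists QEEG band power and the network model among the dependent variables. Step 4 of III.e plans paired and independent analyses, "using the t-test for comparison within each group and between intervention groups", before and after intervention. It does not name outcomes, but Step 3 refers to the outcome variables generally, so I read Step 4 as covering the EEG measures. It does not say which of the two comparisons carries the conclusion.

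**The concern.** A paired test asks whether the second recording differs from the first. Here the first is a rest before any task, and the second is a rest after two task blocks and a 20-minute session. A change in the active arm could come from stimulation, from having just done a task, from two rounds of task exposure, or from time and fatigue. The paired test cannot separate these.

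The protocol presents Go/No-go as a test of prefrontal inhibitory control (I.b.1, II), and stimulation is applied over the dorsolateral prefrontal cortex. Task carry-over could therefore plausibly appear where a stimulation effect is looked for. The EEG measures serve two of the four specific objectives, and section II says they will assess possible prefrontal activation after tDCS. A significant paired change in the active arm could be read as that activation. III.f, on bias, does not mention the difference in state.

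**Working it through.** **Plan's own figure.** The only computed figure is the sample size, 25 per group, which concerns Go/No-go performance. It can be reproduced for some base rates (for example 10% versus 50%, two-sided 0.05, power 0.80, with continuity correction: 25 per group). The protocol has no EEG calculation, and this point does not depend on the sample-size figure.

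**Step 1: what each comparison estimates.** Use a simple additive model (my assumption). S is the stimulation effect, T the immediate post-task carry-over, C the effect per completed task block, and D the drift between the two EEGs. D' is the drift over the shorter interval if the baseline EEG is moved to after the baseline tasks.

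| Order | Active-arm change | Sham-arm change | Active minus sham |
|---|---|---|---|
| As in III.d | S + T + 2C + D | T + 2C + D | S |
| Baseline EEG moved | S + C + D' | C + D' | S |

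The between-arm difference is S in both rows. The within-arm change equals S in neither row unless the nuisance terms are zero. Moving the baseline EEG cancels T but leaves C and D'.

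**Step 2: how often a paired test is significant with S = 0.** Let d be the total nuisance shift in SD units and r the pre-post correlation (both assumed). The SD of the change is √(2(1−r)), and the non-centrality is d√n / √(2(1−r)) with n − 1 degrees of freedom, two-sided 0.05.

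- n = 30 (III.d), d = 0.3, r = 0.6: SD of change 0.894, non-centrality 1.84, significant in 43%.
- n = 30, d = 0.3, r = 0.8: SD of change 0.632, non-centrality 2.60, significant in 71%.
- n = 30, d = 0.2: 22% (r = 0.6) to 39% (r = 0.8).
- n = 30, d = 0.1: 9% to 13%.
- n = 25 (the protocol's size before the drop-out allowance), d = 0.3: 36% to 62%.

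**Step 3: both comparisons together.** Simulation of 4,000 trials with 30 per arm, S = 0, T = 0.3, C = 0.1 and D = D' = 0.1. Between-participant SD is 0.7 and within-participant SD 0.5, so the SD of the change is √(2 × 0.5²) = 0.707. All of these values are assumed.

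| Order | Mean within-arm change | Paired test significant | Between-arm test significant |
|---|---|---|---|
| As in III.d | 0.3 + 0.2 + 0.1 = 0.60 | 99% | 4.8% |
| Baseline EEG moved | 0.1 + 0.1 = 0.20 | 33% | 4.7% |

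Only with C and D also zero does the paired test after the move return to its nominal level (5.2%).

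**Step 4: what baseline adjustment does to the between-arm comparison.** With equal variances, and relative to a test on post values alone (1), the variance is 2(1−r) for change scores and 1−r² for ANCOVA.

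- r = 0.6: 0.80 for change scores, 0.64 for ANCOVA.
- r = 0.8: 0.40 for change scores, 0.36 for ANCOVA.

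ANCOVA with the baseline already collected is therefore no less precise than either unadjusted choice at these correlations.

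**The case against.** The strongest reply is that nothing important is damaged. Objective I.b.1 compares tDCS with sham, both arms follow one sequence, and Step 4 already includes between-group tests. A within-arm before-after test cannot isolate stimulation in any order, and a resting baseline before any task is a defensible choice. This stands, and it limits the point to the within-group tests. It does not dispose of them: Step 4 puts them alongside the between-group tests without saying which one decides.

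Three stronger readings are tempting, and the protocol supports none of them.

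- *That the order biases active versus sham.* It does not. The nuisance terms cancel between randomised arms under the additive model. If tasks after stimulation modify its effect, that interaction stays in the second EEG in either order.
- *That moving the baseline EEG cures the problem at no cost.* The move cancels only the immediate post-task term: the second EEG would still follow two task blocks and the first only one. It also removes the only pre-task resting EEG, which serves the descriptive aims in I.b.2 and I.b.3. And the baseline Go/No-go tasks would no longer follow the rest recording.
- *That matching the state buys precision.* If it raised r from 0.7 to 0.8, the ANCOVA variance would fall by 29% (0.36/0.51 = 0.71); from 0.6 to 0.7, by 20% (0.51/0.64 = 0.80). Nothing in the protocol suggests that r would rise, and Step 4 as written has no baseline adjustment through which to gain.

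It is also fair to say that persistence of a task effect into a rest recording, mostly with eyes closed, is assumed. Even without it, task repetition and elapsed time remain in the paired change.

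**Conclusion.** The point holds for the within-group EEG tests only. As III.d and Step 4 stand, a significant paired change in QEEG or network measures, in either arm, cannot be attributed to stimulation. The size depends on unknowns. For assumed nuisance shifts of 0.2 to 0.3 SD and correlations of 0.6 to 0.8, a paired test in 30 participants with no stimulation effect is significant in 22% to 71% of trials, against a nominal 5%. The protocol gives no EEG variance, correlation or task effect to narrow this range. The conclusion also takes the second EEG to follow the second tasks, as the sentence order suggests. The randomised active-versus-sham comparison remains valid, so this is a matter of which test carries the EEG conclusions and not a flaw in the trial's main contrast.

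**What to change.** In Step 4 of III.e, state that conclusions on QEEG and network outcomes rest on the between-arm comparison of the post-stimulation EEG adjusted for the baseline EEG (ANCOVA), and that within-arm EEG changes are descriptive only. If the normality check fails, keep the baseline adjustment on a transformed or rank scale instead of dropping it. This uses data already planned, adds no procedure or participant time, and costs a sentence or two.

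In III.d, state outright that the second EEG follows the second task block, if that is intended.

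Moving the baseline EEG to after the baseline tasks can be considered but is not needed. It would match the immediate post-task state of the two recordings, at the price of the pre-task resting EEG for I.b.2 and I.b.3 and a 5-minute recording between the baseline tasks and stimulation. If it is done, within-arm changes should still be descriptive.
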